#### Part 2: health-economic evaluation

##### Cost-utility and cost-effectiveness analysis

The health-economic evaluation will be conducted from a societal perspective with a time horizon of 12 months. In the base case analysis, both an incremental cost-utility ratio (ICUR) and an incremental cost-effectiveness ratio (ICER) will be calculated for the cost-utility and cost-effectiveness analysis respectively. The ICUR will be estimated as the total societal costs difference (both informal caregiver and PwD) divided by the sum of the difference in informal caregiver EQ-5D-5L-based quality-adjusted life-years (QALYs) and PwD proxy-rated EQ-5D-5L-based QALYs between the intervention and control arm. The ICER will be estimated as the difference in total societal costs between the intervention and the control arm and will be divided by the difference in effect in terms of QOL-AD change from the baseline score between the intervention and the control arm.

Total costs will be calculated in Euros (€) from a societal perspective and will include intervention and healthcare costs. The costs will be calculated by multiplying each care use outcome from the RUD instrument by its unit price, over the 12-month period (baseline to the last follow-up measure). Unit prices will be based on the Dutch guidelines for cost calculations in healthcare [31] or other sources if not included in the guidelines. The friction cost approach will be used to estimate the lost productivity costs of the informal caregiver, using the measurements of productivity loss as obtained by the RUD. During the analysis, discounting will be applied for the 12-month follow-up. The discount rates will be based on the Dutch cost guidelines with 4% for costs and 1.5% for QALY’s [31]. Finally, as the recall period of most items of the RUD instrument is shorter than the time between measurements, linear interpolation will be used between cost estimates at the follow-up moments. The intervention costs will be calculated based on the estimated costs for (1) the PiB coach training for professionals, (2) the coaching activities of the professional, and (3) the PiB license costs of €200 for each participant (which covers all other intervention costs, e.g., PiB IT system). To calculate the costs for the training and coaching activities, the standard unit prices for the professional will be multiplied by the time required for the training and the mean time spent on all coaching and training activities during the trial.

To calculate the QALYs, the health conditions derived from the EQ-5D-5L will be expressed in utility scores. The Dutch value set for utility scores [44] will be adopted. Hereafter, the QALYs will be calculated by weighing the length of the time spent in a particular health state by the utility at each measurement point, using linear interpolation between measurements.

To handle the uncertainty surrounding the ICUR and the ICER, bootstrapping with 5000 replications will be used to estimate 95% bootstrap intervals around cost and QALY differences. The incremental (difference between control and intervention) outcome (12-month QOL-AD effect, total QALYs, and total costs) will be estimated using a mixed GLM using the outcome as the dependent variable, and trial arm and baseline value (baseline QOL-AD, baseline utility, and baseline 3-month costs, respectively) as independent variables. A random intercept will be employed to acknowledge the hierarchical structure of the data (observations clustered within professionals). Uncertainty surrounding the ICUR and ICER will be graphically presented on a cost-effectiveness plane. A cost-effectiveness acceptability curve will show the probability that the intervention is cost-effective in comparison with usual care for a range of willingness-to-pay values.

Missing data will be handled using the guidance from Faria and colleagues [45]. Any missing follow-up data will be tested for conditionality of observed factors at baseline and missingness status at each observation will be tested for conditionality on observed factors at the previous observation. If missingness is only conditional on baseline factors, baseline missing is limited and missingness is not disaggregated (e.g., mostly all or none of the scales are missing at an observation), it will be handled using inverse probability of censoring weights. If missingness is conditional on previous observation it will be handled using multiple imputations.

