#### Part 2: health-economic evaluation

The health-economic evaluation consists of two primary objectives: (1) to estimate the within-trial cost-utility and uncertainty of PiB compared to usual care from a societal perspective over a time horizon of 12 months using EQ5D5L-based quality-adjusted life years and care use from both caregiver and PwD summed, and (2) to conduct a budget impact analysis. We expect PiB to be cost-effective. In addition, the health-economic evaluation includes the three following secondary objectives: (1) to estimate the within-trial cost-effectiveness and uncertainty of PiB compared to usual care from a societal perspective over a time horizon of 12 months, with effectiveness measured in terms of QOL-AD; (2) to perform a cost-consequence analysis to describe all relevant health outcomes, quality of life, and disaggregated costs categories; (3) to explore the health-economic outcomes of PiB over 24 months; and (4) to estimate the lifetime cost-utility and uncertainty of PiB compared to usual care from a societal perspective using a decision-analytic model with extrapolated trial effects.

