##### Decision-analytic model

An illness-death Markov model will be used to simulate the lifetime cost-effectiveness related to the institutionalization of the person with dementia over a lifetime period. The model will be developed by combining the results from the trial with published estimates on quality of life, care cost, and mortality in dementia. If institutionalization occurs frequently during the trial follow-up period, a parametric survival model will be fitted to the institutionalization data in the control and intervention arm, and the survival model will be used to extrapolate institutionalization over a lifetime. If insufficient observations, a published Dutch institutionalization rate will be multiplied by published relative risks of caregiver outcomes on institutionalization (such as caregiver burden or perseverance time) to the power of observed trial effect on those caregiver outcomes. This will provide a plausible translation of the caregiver outcomes to prevent the institutionalization of the person with dementia.

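### The article's only discounting rule is tied to a base case that ends at 12 months; the effect is small, but the sentence should be corrected and should cover the longer horizons

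*Protocol article*

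**What the plan says.** All references are to the Protocol article.

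- **Horizon.** Under Cost-utility and cost-effectiveness analysis, "The health-economic evaluation will be conducted from a societal perspective with a time horizon of 12 months". The primary objective in Part 2 agrees: "from a societal perspective over a time horizon of 12 months using EQ5D5L-based quality-adjusted life years".
- **Costs.** The same analysis section sums them "over the 12-month period (baseline to the last follow-up measure").
- **Discounting.** That section then states "During the analysis, discounting will be applied for the 12-month follow-up", followed by "The discount rates will be based on the Dutch cost guidelines with 4% for costs and 1.5% for QALY"s. No other discounting statement appears in the article.
- **Longer horizons.** The secondary objectives of Part 2 include "to explore the health-economic outcomes of PiB over 24 months" and "to estimate the lifetime cost-utility and uncertainty of PiB compared to usual care from a societal perspective using a decision-analytic model". The Decision-analytic model section describes an illness-death Markov model to "simulate the lifetime cost-effectiveness related to the institutionalization of the person with dementia over a lifetime period". None of these texts mentions discounting.

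**The concern.** Annual discount rates bring later years back to the value of the first. The rule here names the one period that, under the usual annual convention, needs no discounting, and the analyses that do contain later years have no rule attached.

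Three things follow if a programmer applies the sentence literally:

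1. Costs and QALYs carry different rates, so the primary ICUR moves by rule and not because of data.
2. The size of the move depends on how discounting is done within the year (continuously, at the end of each measurement interval, or at year end). The article does not say which.
3. Rates are given for costs and QALYs only. The QOL-AD ICER would have a discounted numerator and a denominator with no stated rate.

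**Working it through.** The article gives no discount factor, discounted total or ICUR, so there is no figure of its own to reproduce. The check is what the stated rates do.

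**Inputs from the article.** Rates r = 0.04 (costs) and r = 0.015 (QALYs); base-case horizon 12 months; follow-up measurements at 3, 6 and 12 months within it.

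**Assumption not in the article.** Incremental costs and QALYs accrue evenly over the period, except where noted.

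**Step 1: the 12-month base case.** An amount at time t (years) is multiplied by (1+r)^-t. The ICUR is multiplied by the cost factor divided by the QALY factor.

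- Continuous: mean factor = (1 - (1+r)^-1) / ln(1+r).
- Interval end: 0.25(1+r)^-0.25 + 0.25(1+r)^-0.5 + 0.5(1+r)^-1.
- Year end: 1/(1+r).

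| Convention | Costs | QALYs | ICUR multiplied by | Change |
|---|---|---|---|---|
| Continuous | 0.981 | 0.993 | 0.988 | -1.2% |
| Interval end | 0.973 | 0.990 | 0.983 | -1.7% |
| Year end | 0.962 | 0.985 | 0.976 | -2.4% |
| Year 1 undiscounted | 1.000 | 1.000 | 1.000 | 0 |

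**Step 2: early costs.** The programme runs 8 to 12 weeks, so the cost difference could fall almost wholly in the first 3 months. Placing it at the midpoint of that period (t = 0.125) gives a cost factor of 1.04^-0.125 = 0.9951. With QALYs still accruing evenly (0.9926), the ICUR is multiplied by 0.9951/0.9926 = 1.0025, about +0.3%. The sign therefore depends on when costs and QALYs arise.

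**Step 3: the QOL-AD ICER.** With no rate for the effect, the ratio moves with the cost factor alone. With even accrual that is 0.981 to 0.962, or -1.9% to -3.8%.

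**Step 4: where discounting matters more.** Leave year 1 undiscounted and use annual steps: mean factor over T years = (1/T) × sum of (1+r)^-k for k = 0 to T-1. The article gives no length for the lifetime model, so 5, 8 and 10 years of even accrual are illustrations only.

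| Horizon | Costs | QALYs | ICUR multiplied by |
|---|---|---|---|
| 24 months | 0.981 | 0.993 | 0.988 |
| 5 years | 0.926 | 0.971 | 0.954 |
| 8 years | 0.875 | 0.950 | 0.875/0.950 = 0.921 |
| 10 years | 0.844 | 0.936 | 0.901 |

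So a rule about discounting matters little over 24 months (about 1%) and noticeably over a model horizon of several years.

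**The case against.** **Discounting inside a year is not an arithmetic error.** This stands. Discounting from time zero is coherent. It departs from the annual convention, and whether the cited Dutch guideline excludes the first year cannot be checked from the article.

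**The effect on the primary result is trivial.** This stands too. The shift is between about -2.4% and +0.3% under the timings examined. A reader might infer that the rule tilts the ICUR in favour of PiB; the article does not support that, because the direction depends on timing.

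**The longer analyses may well be discounted.** A reader might infer that the 24-month and lifetime results will be left undiscounted. The article does not say so. The rule sits under the within-trial heading, the sentence giving the rates is not itself limited to 12 months, and the lifetime model gets one condensed paragraph. The full protocol or analysis plan, which is not shown, may settle it. The figures in Step 4 therefore show why the rule belongs there; they are not an error in a planned result.

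**It may be only a wording slip** for discounting beyond the 12-month follow-up. That is plausible, but the sentence still needs correcting. It is a positive instruction attached to the primary economic analysis, and someone coding from it would discount the base case.

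**Conclusion.** The point holds as a minor misstatement. The article's single discounting rule is assigned to an analysis that ends at 12 months, where under an annual convention it has nothing to act on. Taken literally, it changes the primary ICUR by about -1.2% to -2.4% with even accrual, or about +0.3% if the cost difference falls in the first 3 months. It also discounts only the numerator of the QOL-AD ICER (-1.9% to -3.8% with even accrual). None of this is likely to reverse a cost-effectiveness conclusion.

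On the 24-month and lifetime analyses the article is silent; no error in them is shown. The sizes rest on the stated rates and on assumed timing, which the article does not give.

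**What to change.** Replace the discounting sentence with: 'Costs and QALYs in the first 12 months are not discounted; in the 24-month analysis and the lifetime model, costs and QALYs accruing after month 12 are discounted at 4% and 1.5% per year.'

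This makes the horizon, the objectives and the model section consistent. It also removes the unstated within-year convention and the mismatch in the 12-month QOL-AD ICER. If discounting within the first year is really intended, the plan should say so, give the within-year convention and the reason for it, and state how the QOL-AD effect is treated.

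The cost is one sentence. No new data are needed, and the base-case code loses a step.

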##### Decision-analytic model

An illness-death Markov model will be used to simulate the lifetime cost-effectiveness related to the institutionalization of the person with dementia over a lifetime period. The model will be developed by combining the results from the trial with published estimates on quality of life, care cost, and mortality in dementia. If institutionalization occurs frequently during the trial follow-up period, a parametric survival model will be fitted to the institutionalization data in the control and intervention arm, and the survival model will be used to extrapolate institutionalization over a lifetime. If insufficient observations, a published Dutch institutionalization rate will be multiplied by published relative risks of caregiver outcomes on institutionalization (such as caregiver burden or perseverance time) to the power of observed trial effect on those caregiver outcomes. This will provide a plausible translation of the caregiver outcomes to prevent the institutionalization of the person with dementia.

##### Budget impact analysis

A budget impact analysis will be performed based on the recommendations from Sullivan et al. [46] In the budget impact analysis, the effectiveness of the intervention will be extrapolated over 3 years. Perspectives that will be considered are the societal and the government (in the Netherlands: Budget Kader Zorg) perspectives. Different implementation scenarios (ranging from 0 to 100% implementation) will be evaluated. The total number of participants eligible for the intervention will be estimated based on Dutch epidemiological data. Resource utilization will be calculated by multiplying the number of eligible participants with the resource utilization rates obtained from the health-economic evaluation. Different prices will be used to value resource use depending on the perspective of the analysis: Dutch standard costs from the societal perspective and actual Nationaal Zorg Autoriteit (NZA) tariffs from the government perspective. Both resource use and annual costs will be presented over a 3-year period for all perspectives. Aggregated and disaggregated (e.g., medical care, secondary care, and productivity losses) total costs per year will be presented for the different perspectives and scenarios.

#### Process evaluation (part 3)

In addition to the cluster RCT, a process evaluation will be performed to evaluate the internal and external validity. In a previous study on PiB, an extensive process evaluation has been conducted [47]. Therefore, to avoid overburdening participants, a shortened version of that process evaluation will be used to evaluate the intervention and sampling quality.

The sampling quality will be evaluated via the descriptions of (1) the recruitment procedure, (2) the informed consent procedure, (3) the allocation and randomization procedures, and (4) the methodology of the shared control arm. This data will be obtained from the research database. Additionally, the experienced facilitators and barriers to the recruitment of informal caregivers will be collected via a self-developed online survey completed by the care professionals involved in participant recruitment. Finally, the reach will be calculated by comparing the number of participating informal caregivers to the total number of approached individuals.

For the intervention quality, (1) general satisfaction and (2) treatment fidelity will be evaluated. The general satisfaction will be collected via a self-developed online questionnaire, which caregivers and care professionals will be asked to complete after the eight-week intervention. Treatment fidelity will be collected via a self-developed questionnaire for the informal caregivers and care professionals which will ascertain the extent to which they were able to follow or provide the intervention as planned. This will be combined with website monitoring in the form of clickstreams to determine the complete treatment fidelity of the coach and user. Finally, based on a recommendation to enhance treatment fidelity [48], all informal caregivers will be asked at all measuring moments whether they had received a similar caregiver support program in the past year to ensure that no participants received a similar intervention during the trial duration that might have influenced their outcomes.

### Data monitoring and adverse events

The Medical Ethics Review Committee of Maastricht University stated that the study does not need a full review according to the Dutch Medical Research with Human Subjects Law (WMO) which means that the study brings a very low health risk for participants. For this reason, a data monitoring committee will not be needed for this trial, and adverse events will not be formally monitored. However, information on death, hospitalization, and institutionalization is structurally collected and will provide insight into these serious adverse events.

### Protocol modifications

Protocol amendments and relevant changes will be communicated to the local ethical committee of the University of Maastricht and the sponsor. Additionally, these changes will also be updated in the trial registration (ClinicalTrials.gov, NCT05450146).

### Dissemination plans

The results from the trial will be shared with the scientific community by publishing the study results in international peer-reviewed open-access scientific journals and updating the trial registration (ClinicalTrials.gov, NCT05450146). In addition, the results will be communicated with the trial sponsor, study participants, care professionals, health service providers, and the dementia networks in the Netherlands. For future articles, the International Committee of Medical Journal Editors (ICMJE) guidelines [49] will be used for authorship eligibility and there is no intended use of professional writers. After the research, the research syntaxes and an anonymized version of the data will be made available for reuse upon reasonable request.

## Discussion

In this paper, the design of a cluster RCT was described aimed to evaluate the effectiveness and cost-utility/cost-effectiveness of the PIB blended care program for informal caregivers of PwD.

During the preparation of the trial, several alternative study designs have been considered by the research team, mainly in terms of their validity and practicality. A stepped-wedge design would probably have increased willingness to participate because all participants would have received the PiB intervention. However, it was not preferred due to the long follow-up period leading to participants of the control arm to no longer being in the targeted early dementia stage when starting the PiB program. In addition, a long delay in the treatment time after inclusion could have significantly reduced power [50], and a stepped-wedge design was considered impractical considering the shared control arm. A three-arm randomization design (control arm, PiB intervention arm, and intervention arm from the collaborating study) was considered but not adopted because we expected professionals to prefer either the PIB intervention or the collaborating study intervention. If a professional is allocated to a (strongly) unpreferred intervention, this could negatively impact recruitment and the intervention’s performance. Finally, an RCT with randomization at the individual level was considered for its gold standard in research. However, it was disregarded because of its risk of contamination [51, 52], which would negatively affect the reliability and validity of the study [53]. This contamination could occur when a professional trained for the PiB intervention also provides care for a participant in the control arm. After considering these designs, the research team concluded that a cluster-randomized controlled trial design was the optimal balance between validity and practicality.

For trials with cluster randomization, the potential for selection bias is high because the allocation to treatment is usually predetermined for each member of the cluster, which is a common but undesired practice [53, 54]. This could be demonstrated when a care professional who has foreknowledge of their allocation to the PiB intervention arm likely approaches potential participants in a different way than a care professional who known has been allocated to the control arm. Therefore, in this study, clusters will be randomized after inclusion and baseline measurement to eliminate foreknowledge that can lead to selection bias. During the randomization process, stratified randomization will be used to limit potential selection bias due to a possible association between the organization and the impact of the care received by the informal caregiver [23].

The shared control group will increase the feasibility of the recruitment of participants, which is often a serious challenge in research. However, a shared control group also brings a risk of selection bias. We expect that the participants in the collaborating study are a slightly different selection of the same target population for the following reasons: (1) they will be recruited through a different type of collaborating organizations and (2) they might have different participation considerations for the collaborating study, considering it will be a peer-based group intervention. To prevent this selection bias, matching will be executed to control for these anticipated differences.

The study may yield some limitations. A limitation is that the PiB intervention is only aimed at informal caregivers with internet skills. Therefore, the results of this study will not be generalizable to all informal caregivers. Another limitation is that, due to the nature of the intervention, participant and care professional blinding was considered not feasible by the research team. The absence of blinding could lead to a placebo effect.

In conclusion, the results of this research will add to the scientific knowledge of the effectiveness of the blended care intervention “Partner in Balance.” The program is hypothesized to improve informal caregivers’ self-efficacy and is expected to be cost-effective. This study will provide valuable insights to informal caregivers, PwD, policymakers, care insurers, and care professionals into the effectiveness of PiB for supporting informal caregivers of PwD.

